**eAppendix 1. Statistical Analysis Plan**

The study aims to compare the effectiveness of Ureteroscopy (URS) and shockwave lithotripsy (SWL) as surgical treatments for kidney stone removal and patient experience in pediatric patients. The primary outcome is stone clearance, defined as the absence of any stone with a longest dimension greater than 4mm in an ultrasound (US) scan performed within 4-8 weeks post-surgery. If multiple images are available, the one closest to 6 weeks will be used. Secondary outcomes include patient experiences measured by patient-reported outcomes (PROs) using 5 PROMIS domains, DVSS, and QUIKSS at baseline (before surgery), and at 1 week (7 days +/- 3 days), 3 weeks (21 days +/- 7 days), 6 weeks (45 days +/- 7 days), and 3 months (90 days +/- 7 days) after surgery. We used propensity scores and inverse-probability-weighting adjustment to reduce treatment-selection bias when comparing outcomes.

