### Outcome model

Both the primary and secondary outcomes were compared using the IPW approach. The outcomes were compared using regression models with IPW and adjusted for unbalanced confounders after weighting. The analysis of PROs was conducted at 1-week, 3-weeks, 6-weeks, and 3-months after the index surgery adjusting for baseline scores.

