### Missing data

We used multiple imputation (MI) to handle missing data. Variables used to impute missing data included all baseline covariates, treatment variable, and observed outcomes that were used in the analysis. Twenty imputed datasets were created and analyzed separately, and the results were combined using Rubin's rules to produce valid statistical inferences. MI was used for the analyses of stone clearance, PROs at week 1, and HTE of both primary and secondary analyses.

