### 2.2 Secondary Objectives (or Aim)

The secondary objective is to compare patients' experiences after URS, SWL, and PCNL. We will assess the immediate (within 7-days +/- 3 days) and delayed (21-days +/- 7-days, 45-days +/- 7-days, and 90 days +/- 30 days) impact of surgery on patient-reported outcomes (PROs) selected by PKIDS patient partners. The PROs include the PROMIS, other questionnaires commonly used in studying the impact of kidney stone disease on health states, and urinary tract symptoms. We will examine HTE by age and sex and identify modifiable surgical techniques that impact these experiences for each surgery. We will also determine unplanned hospitalizations, ED visits, and repeat surgeries for the 3 months following each procedure.

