#### **3.2.2 Duration of Study Participation**

The duration of the study for the enrolled patient participants is the time of consent to the end of follow-up within PKIDS. Patient participants will complete questionnaires before surgery (baseline), within 7 days of surgery (+/- 3 days), 21-days +/- 7-days, 45-days +/- 7-days, and 90 days +/- 30 days after surgery. Ultrasound (as part of clinical care) will be obtained 6 weeks (+/- 2 weeks) after surgery. EHR surveillance of ED visits, clinic visits, hospitalizations, and surgeries will occur during the duration of clinical follow-up in PKIDS. Surgeon participants will complete one-time questionnaires assessing individual and institution characteristics.

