#### **4.3.1 Questionnaires**

Patient participants will complete a baseline questionnaire that assesses individual characteristics, including but not limited to past medical history and family history, with particular emphasis on stone factors. Patient participants will complete questionnaires, including PROMIS measures and a urinary symptom questionnaire, before surgery (baseline), within 7 days of surgery (+/- 3 days), 21-days +/- 7-days, 45-days +/- 7-days, and 90 days +/- 30 days after surgery. The questionnaires include, but are not limited to, PROMIS instruments (pain intensity, pain interference, anxiety, psychological stress experiences) and a urinary symptom questionnaire. Questionnaires will be administered electronically and recorded in secure electronic databases including OnCore and REDCap, enabling completion at

---

---

home. For patients who do not have mobile devices or a computer, a member of the research team can administer the questionnaires over the phone or on paper.

Surgeon participants will complete one time questionnaires assessing individual and institution characteristics via REDCap.

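### The SAP analyses the 3-month patient-reported outcomes in a ±7-day window, but the protocol collects them over ±30 days; the two must be reconciled

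*Combined protocol and SAP*

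**What the plan says.** The SAP introduction lists the follow-up PRO assessments "at 1 week (7 days +/- 3 days), 3 weeks (21 days +/- 7 days), 6 weeks (45 days +/- 7 days") and then "3 months (90 days +/- 7 days) after surgery".

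The protocol states the last window differently, and does so four times:
- Section 2.2, secondary objectives: "45-days +/- 7-days, and 90 days +/- 30 days".
- Section 3.2.2, duration of participation: "45-days +/- 7-days, and 90 days +/- 30 days after surgery".
- Section 4.3.1, questionnaires: "21-days +/- 7-days, 45-days +/- 7-days, and 90 days +/- 30 days after surgery".
- Section 5.2, participant questionnaires: the same windows as section 4.3.1.

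Three months is an analysed time point. The SAP's outcome model section says: "The analysis of PROs was conducted at 1-week, 3-weeks, 6-weeks, and 3-months after the index surgery adjusting for baseline scores". In the protocol, section 3.1 ties Aim 2 to experiences at 3 months. Section 6.3.2 plans a separate 3-month model, with slope and area-under-the-curve comparisons over time. Section 6.4 counts 3 months in the Bonferroni family.

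On missing data, the SAP first says in general terms that multiple imputation was used, and then gives its scope: "MI was used for the analyses of stone clearance, PROs at week 1, and HTE of both primary and secondary analyses".

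**The concern.** The two documents agree on the 1-week, 3-week and 6-week windows and part only at 3 months. Neither explains the difference. A questionnaire returned on day 70 or day 110 is valid under the protocol, yet it is outside the period in which the SAP defines the 3-month outcome.

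If the SAP window is applied as written, such questionnaires leave the main 3-month comparison. Imputation is not listed for that comparison, so it would apparently rest on the remaining complete cases. The cost is precision, given up on data already collected from participants. If the SAP window was not applied, a reader still cannot tell which days the 3-month results represent.

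The SAP handles timing more carefully for ultrasound. There it gives a selection rule (the image closest to 6 weeks) and a widened-window sensitivity analysis (0 to 16 weeks). It gives neither for the PROs.

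**Working it through.** The documents give no count of 3-month questionnaires by completion day, so there is no figure of theirs to reproduce. The check has four parts.

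**1. Windows side by side**

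| Assessment | SAP introduction | Protocol 2.2, 3.2.2, 4.3.1, 5.2 |
|---|---|---|
| 1 week | 7 ± 3 | 7 ± 3 |
| 3 weeks | 21 ± 7 | 21 ± 7 |
| 6 weeks | 45 ± 7 | 45 ± 7 |
| 3 months | 90 ± 7 | 90 ± 30 |

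**2. Share of days**
- SAP window: days 83 to 97, 2 × 7 + 1 = 15 days.
- Protocol window: days 60 to 120, 2 × 30 + 1 = 61 days.
- Protocol-valid days outside the SAP window: 61 − 15 = 46, and 46/61 = 75.4%. On a continuous scale, 1 − 14/60 = 76.7%.

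**3. Share of questionnaires, under assumed completion times**

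This depends on when participants respond, which the documents do not report. Assume completion days are normal around day 90 with standard deviation s, truncated to days 60 to 120. Then

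share outside = 1 − [Φ(7/s) − Φ(−7/s)] / [Φ(30/s) − Φ(−30/s)].

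| s (days, assumed) | Share outside the SAP window |
|---|---|
| 5 | 16% |
| 7 | 32% |
| 10 | 48% |
| 15 | 62% |
| 20 | 68% |
| 30 | 73% |

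As a worked case, for s = 10 the numerator is 0.516 and the denominator 0.997, so the share outside is 1 − 0.517 = 48%.

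Other assumed patterns give other answers. An even spread over days 60 to 120 gives 75%. With an exponential delay after a fixed send date, cut off at day 120, the results for mean delays of 7 and 14 days are:
- sent on day 83: 13% and 32%;
- sent on day 90: 36% and 55%;
- sent on day 60: 97% and 88%.

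**4. What this does to precision**

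If the same fraction f is kept in each arm, the standard error grows by about 1/√f. With 16% outside, 1/√0.84 = 1.09. With 48% outside, 1/√0.52 = 1.39. With 73% outside, 1/√0.27 = 1.92. Equal fractions in the arms are an assumption.

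**The case against.** The strongest reply is that the SAP sentence is only an introductory list of time points. It contains no rule that excludes an out-of-window questionnaire or sets it to missing. The ± 7 repeats the window of the two preceding assessments, so a drafting slip fits the text as well as an applied filter does. An analysis window narrower than the collection window is also a legitimate choice if it is stated and justified. Finally, the reach is narrow: this is one of four follow-up points of a secondary outcome, and the PRO results in the supplement (eTables 8 to 10) are all at 1 week.

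Most of this stands, and it limits the point without removing it. A slip still needs correcting, and a deliberate narrowing would need a reason that the SAP does not give.

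Four stronger readings are tempting, and the documents do not support them:
- **That three-quarters of the questionnaires are lost.** The 46/61 is a share of days. It becomes a share of questionnaires only if returns are spread evenly over days 60 to 120. It is not a ceiling either: the share could in principle lie anywhere from 0% to 100%.
- **That the retained sample would be the prompt responders.** The window is symmetric about day 90 and drops days 60 to 82 as well as days 98 to 120. No send date is given. If questionnaires opened on day 60, the promptest would be the ones left out.
- **That imputation of PROs is confined to week 1.** The list also includes the heterogeneity analyses of the secondary outcomes. What can be said is that the main 3-month comparison is not named.
- **That percutaneous nephrolithotomy (PCNL) would suffer most.** It is the smaller enrolled group (93 against 946 for ureteroscopy in eTable 4), but no 3-month PRO counts by arm are given.

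**Conclusion.** The contradiction is certain: the SAP says 90 ± 7 days once, and the protocol says 90 ± 30 days four times, for an assessment that both documents analyse. About 75% of the protocol-valid days fall outside the SAP window.

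The effect on the data is conditional. It requires that the SAP window be applied as written, and its size rests on a completion-time distribution that must be assumed. For normal returns centred on day 90 the share lost is roughly 16% to 73%, and the patterns with a fixed send date widen that range. Loss of precision is the supported consequence; a bias in a particular direction is not. No estimate reported in these documents is shown to depend on the ± 7 window.

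The point is worth acting on because it concerns a stated outcome definition and the correction is cheap.

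**What to change.** Reconcile the SAP introduction with protocol sections 2.2, 3.2.2, 4.3.1 and 5.2:
- Set the SAP's 3-month analysis window to the protocol's collection window, 90 ± 30 days, using the questionnaire closest to day 90 if there is more than one. This does not collide with the 6-week window, which ends on day 45 + 7 = 52, before day 60.
- Keep ± 7 days as a sensitivity analysis.
- State which window was applied and how questionnaires from days 60 to 82 and 98 to 120 were handled.
- Report by arm how many 3-month questionnaires fall in each window.

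If ± 7 is only a drafting slip, the cost is one number in the SAP plus the table of counts. If it was applied, the 3-month PRO models must be re-run on data already in hand. The downside is slightly more spread in assessment timing, which the ± 7 sensitivity analysis would show.

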**Study unit and assessment of treatment**

The primary outcome, stone clearance, is assessed at the kidney level, with the treatment defined as the first surgery performed on each kidney. For the secondary outcomes, the PROs, the study unit is the patient, with the treatment defined as the patient's first surgery.

**Propensity score model**

A logistic regression model was used to estimate the propensity scores for receiving treatment. The construction of the propensity score model involved selecting confounders from a large pool of candidates related to treatment selection. These candidates included baseline characteristics (37 variables), patient conditions from the pre-op form (12 variables), stone characteristics from the pre-op imaging form (13 variables), surgery-related characteristics from the surgery form (27 variables), and institutional and surgeon demographics (62 variables). The pool of candidate confounders was pre-screened based on the clinical importance scores provided by domain experts in the Data and Outcomes Committee (DOC), which included the study PI, site PIs, and statisticians. Variables were also assessed for their correlation with other variables. Within each category, variables were ranked based on their clinical importance and correlation scores. Correlation scores were defined by the number of correlated variables with a correlation coefficient greater than 0.3, considered moderate correlation (Cramér's V of 0.3). Variables that were less important or highly correlated with higher-ranked variables were removed. Specifically, we started from the top of the list and removed variables if they had a correlation coefficient exceeding 0.4 with higher-ranked variables, (a Cramér's V of 0.5 is considered strong correlation), while retaining the variable with higher clinical importance. This procedure, conducted without analyzing the outcome data, yielded a list of pre-screened confounders. The pre-screened confounders were further examined using univariate analysis to evaluate their associations with the surgical treatment across all enrolled participants in the study. Variables with a p-value less than 0.2 were selected and reviewed by the DOC. The final list of confounders was determined by the DOC, combining domain knowledge with the estimated strength of association. The list is shown in Table 1. We verified the performance of the propensity score model by comparing the distribution of confounders between treatment groups both before and after inverse probability weighting (IPW). Confounders with a standardized difference in median (SDM) greater than 0.25 after weighting were included in the outcome models for further adjustment.

**eTable 1.** Final List of Confounders Used in the Propensity Score Model

| Domains                                   | Variables                                                                                                                                                                                                                                                                                                                                                                                                                                                                                                                      |
|-------------------------------------------|--------------------------------------------------------------------------------------------------------------------------------------------------------------------------------------------------------------------------------------------------------------------------------------------------------------------------------------------------------------------------------------------------------------------------------------------------------------------------------------------------------------------------------|
| Baseline Characteristics                  | experience with prior surgery, problems with blood cells, muscle problems                                                                                                                                                                                                                                                                                                                                                                                                                                                      |
| Pre-op variables                          | age, prior GU reconstruction, monogenic stone disease                                                                                                                                                                                                                                                                                                                                                                                                                                                                          |
| Surgery variables                         | structural renal abnormality, primary clinical indication for surgery, surgery within 24 hours of symptom evaluation, restrictions to OR access                                                                                                                                                                                                                                                                                                                                                                                |
| Imaging variables                         | imaging type, number of stones, stone location, stone size                                                                                                                                                                                                                                                                                                                                                                                                                                                                     |
| Institutional and surgeon Characteristics | number of kidney stone patients evaluated in outpatient clinic during 2018-2019, the importance of patient age in surgeon's surgical decision-making, the importance of family's preference in surgeon's surgical decision-making, the importance of stone size in surgeon's surgical decision-making, the importance of availability of equipment in surgeon's surgical decision-making, surgeon's preference for URS versus PCNL for a 1.5 cm kidney stone, surgeon's preference for SWL versus PCNL for a 2 cm kidney stone |

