|                                                            | Calyceal Diverticulum  | 0
(0.0)           | 0
(0.0)                   | 23
(2.4)           | 10
(2.3)                   |
|                                                            | Other (not specified)  | 3
(3.2)           | 3
(6.5)                   | 37
(3.9)           | 13
(3)                     |
|                                                            | Missing/Unknown        | 2
(2.2)           | 1
(2.2)                   | 8
(0.8)            | 3
(0.7)                    |
| Comorbid conditions, n (%)                          | neurogenic bladder     | 17
(18.3)         | 11
(23.9)                 | 78
(8.2)           | 39
(8.9)                   |
|                                                            | Ventilator dependent   | 6
(6.5)           | 5
(10.9)                  | 11
(1.2)           | 8
(1.8)                    |
|                                                            | Neuromuscular disorder | 33
(35.5)         | 18
(39.1)                 | 116
(12.3)         | 52
(11.9)                  |
|                                                            | Hematologic disorder   | 9
(9.7)           | 3
(6.5)                   | 42
(4.4)           | 23
(5.3)                   |

**eTable 4.** Characteristics of the Enrolled and Primary Analytic Cohorts of Patients Who Underwent Percutaneous Nephrolithotomy (PCNL) and Ureteroscopy (URS)

| Characteristics        |                            | PCNL                 |                              | URS                   |                               |
|------------------------|----------------------------|----------------------|------------------------------|-----------------------|-------------------------------|
|                        |                            | Enrolled Cohort (93) | Primary Analytic Cohort (46) | Enrolled Cohort (946) | Primary Analytic Cohort (436) |
|                        | Oxygen support             | 9
(9.7)           | 7
(15.2)                  | 25
(2.6)           | 13
(3.0)                   |
|                        | Cardiac risk factors       | 5
(5.4)           | 1
(2.2)                   | 32
(3.4)           | 11
(2.5)                   |

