| Prior kidney stone surgery            | Interventional radiology available                                             |
| Acute/urgent procedure or elective    | SWL machine owned by hospital                                                  |
| Prior diversion for the stone episode | Laser ownership                                                                |
| Ambulatory status                     | Kidney Stone Center                                                            |
| Pre-op imaging type                   | Trainee involvement in surgery                                                 |
| Pre- and post-operative medications   | Free-standing children's hospital                                              |

We will construct propensity score models based on these confounders, and use an inverse probability treatment weighting approach for multi-level data to balance covariates across treatments at patient- surgeon- and hospital-levels in evaluation of overall treatment effect and HTE. As we compare three treatments, we will use multinomial logistic regression with random effects to calculate propensity scores. The random effects will allow us to account for correlation within surgeon- and hospital-levels. We assume there is overlap among the treatment groups such that every patient could have received each treatment. Under this assumption, the weighted treatment effects yield consistent estimates of the population averaged treatment effects, provided that the commonly assumed assumptions of consistency

and no unmeasured confounders in causal inference also hold. We will examine overlap of covariates across treatment groups using plots of distributions of the estimated propensity scores across groups, and examine the balance of covariates using standardized difference in mean before and after weighting. We will also conduct sensitivity analyses using both simulation-based approaches and propensity score-based sensitivity functions to assess the effect of potential unmeasured confounding on the estimates of the parameters of interest.

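### The SAP selects confounders for further adjustment by a standardized difference in median, where the protocol specifies the mean; as written, the rule is blind to most imbalance in yes/no confounders

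*Combined protocol and SAP*

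**What the plan says.** The section of the SAP (eAppendix 1) on the propensity score model compares confounders between treatment groups before and after inverse probability weighting. It then states: "Confounders with a standardized difference in median (SDM) greater than 0.25 after weighting were included in the outcome models for further adjustment". The section on the outcome model applies the result: "The outcomes were compared using regression models with IPW and adjusted for unbalanced confounders after weighting". PRO models also adjust for the baseline score. For stone clearance, no other route to covariate adjustment is given.

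Protocol section 6.3 plans to "examine the balance of covariates using standardized difference in mean before and after weighting". It sets no numerical cut-off.

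Neither document gives a formula for the median-based measure, says how yes/no or nominal variables are handled in it, or explains the move from mean to median.

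eTable 1 lists 21 confounders. Among them are "experience with prior surgery, problems with blood cells, muscle problems"; "age, prior GU reconstruction, monogenic stone disease"; "structural renal abnormality, primary clinical indication for surgery, surgery within 24 hours of symptom evaluation, restrictions to OR access"; and "imaging type, number of stones, stone location, stone size". The other seven describe the institution and the surgeon.

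**The concern.** The rule is meant as a safety net: if weighting leaves a confounder unbalanced, the outcome model adjusts for it. A measure built on medians cannot do that for most yes/no variables. The median of a 0/1 variable is 0 whenever fewer than half the patients have the characteristic, so two arms can differ widely and still show no difference in medians.

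The check matters here. The comparison is not randomized and the arms differ strongly at baseline. The PCNL arm is small, with 46 patients against 436 for URS in the primary analytic cohort (eTable 4), so weighting may not balance everything. If medians were really used, some confounders that needed adjustment in the primary model may have been passed as balanced.

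**Working it through.** The plan derives no figure on this point, so there is none to reproduce. The check is what the rule does with yes/no, nominal and numeric variables.

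**Formulas.** With prevalences p1 and p2, let s = sqrt((p1(1−p1) + p2(1−p2))/2).
- Mean-based difference = (p1 − p2)/s.
- Median-based difference = (m1 − m2)/s, where m = 1 if p > 0.5 and m = 0 if p < 0.5. The SAP gives no formula; using the same s is an assumption. When the medians are equal the result is 0 whatever the denominator.

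**Types of confounder in eTable 1.** Coding is not stated. By name, about 8 appear to be yes/no: the three baseline items, prior GU reconstruction, monogenic disease, structural renal abnormality, surgery within 24 hours and OR restrictions. Three are nominal (indication, imaging type, stone location). Ten are numeric or ordinal (age, number of stones, stone size and the seven institution and surgeon items). 8 + 3 + 10 = 21.

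**Yes/no variables that can be checked.** Enrolled cohort in eTable 4, PCNL (n = 93) v URS (n = 946), before weighting:

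| Variable | PCNL | URS | Mean-based | Median-based |
|---|---|---|---|---|
| Neuromuscular disorder (proxy for muscle problems) | 33/93 = 35.5% | 116/946 = 12.3% | 0.57 | 0 |
| Structural renal abnormality | 21/93 = 22.6% | 112/946 = 11.8% | 0.29 | 0 |
| Hematologic disorder (proxy for blood-cell problems) | 9/93 = 9.7% | 42/946 = 4.4% | 0.21 | 0 |
| Prior stone surgery (proxy for experience with prior surgery) | 23/93 = 24.7% | 160/946 = 16.9% | 0.19 | 0 |

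Example for the first row: s = sqrt((0.355×0.645 + 0.123×0.877)/2) = 0.41, and (0.355 − 0.123)/0.41 = 0.57. At the same 0.25 cut-off the mean-based measure flags the first two rows. The median-based measure flags none.

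**How much can be missed.** A mean-based difference of 0.25 is reached at 10% v 18.7%, or at 20% v 30.8%. Both have a median difference of 0. So does 10% v 49.9%, where the mean-based value is 0.97.

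**The opposite error.** At 49% v 51% the mean-based value is 0.02/0.50 = 0.04, and the median-based value is 1/0.50 = 2.0.

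**Levels of nominal variables.** The result depends on where the prevalences fall, not on how far apart they are:
- Ureteral location, 14.0% v 48.3%: mean-based −0.80, median-based 0.
- UTI as indication, 58.1% v 18.2%: mean-based 0.90, median-based 2.26.
- Non-lower-pole location, 57.0% v 27.1%: mean-based 0.64, median-based 2.13.

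**Numeric variables.** Taking SD as IQR/1.349, the unweighted median-based difference is about 1.42 for largest stone size (15 [9–20] v 6 [4–9] mm), 0.85 for number of stones (2 [1–3] v 1 [1–2]) and −0.15 for age. Here the rule can respond.

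**After weighting.** The protocol targets population-averaged effects, so weighting should pull both arms towards the pooled prevalence: (33 + 116)/1039 = 14% for neuromuscular disorder and (21 + 112)/1039 = 13% for structural abnormality. Both are far below 50%, so the arms would be unlikely to straddle it.

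**Scale, on an assumption.** Suppose 20% v 30.8% remained after weighting, a gap of 10.8 points. If the confounder changes clearance by 10, 20 or 30 points (assumed), the bias is 10.8 × 0.10 = 1.1, 2.2 or 3.2 points. The overall contrast in eTable 13 is −6.4 points (95% CI −22.8 to 10).

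**The case against.** The strongest reply is that median is a slip. The abbreviation SDM fits mean and median equally well, and the protocol says mean. The balance plots in eFigure 4 are not reproduced in the text, so the documents do not settle what was computed. This stands. It also means that the sentence needs correcting either way. The protocol does leave statistical detail to the SAP, so a deliberate change was open to the authors, but no reason for one is given.

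A reader might infer that the rule can never trigger. It can. It responds to numeric confounders, including stone size and number of stones, and it over-responds to indicators that straddle 50%.

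A reader might also infer that the analysis is confounded by the variables in the table above. The documents do not show this. The rule applies after weighting, and these figures are from before it. Muscle problems and structural abnormality are already in the propensity model, three of the four rows are proxies, and no prevalence is given for prior GU reconstruction, monogenic disease, surgery within 24 hours or OR restrictions. Several small biases could also cancel.

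Finally, a reader might want a stricter cut-off such as 0.10. Nothing in the documents supports one. With 46 and 436 patients the chance standard error of a standardized difference is roughly sqrt(1/46 + 1/436) = 0.155, ignoring weighting. At that precision about 52% of perfectly balanced covariates would exceed 0.10.

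**Conclusion.** The SAP and the protocol name different balance measures, and the SAP's version is unsuitable for yes/no and nominal confounders. Read literally, it gives 0 for any yes/no confounder whose weighted prevalences lie on the same side of 50%, even at a mean-based difference as large as 0.97, and about 2.0 for a trivial difference across 50%. This affects about 8 of 21 confounders, with the three nominal ones handled erratically. Since the rule decides which covariates enter the primary outcome model, it should be corrected.

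The conclusion rests on three assumptions: that the eight variables are coded yes/no, that the eTable 4 proxies are adequate, and that weighted prevalences stay below 50%. It is a finding about the rule. Whether medians were actually used, and whether any imbalance remained after weighting, cannot be determined from the text.

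**What to change.** Replace the measure in the SAP with the standardized difference in mean, as in protocol section 6.3. For yes/no and nominal confounders, use the standardized difference in proportion for each level. Give the formula, and keep the stated 0.25 cut-off.

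Then state which measure produced the reported balance results and the list of adjusted confounders.
- If it was the mean-based one, correcting the sentence is enough.
- If medians were used, recompute balance after weighting, update the list of confounders carried into the outcome models and re-run those models.

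The cost is a sentence or two in the SAP and at most one re-run. The downside is possibly a few more outcome-model terms with a small PCNL arm.
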